### Participants’ Recruitment and Subscription

Subscription to the Wellness4Teachers email messaging program will be initiated by individual teachers accepting an invitation to subscribe from the Lusaka Apex Medical University’s organizational account on the ResilienceNHope web-based application. The local principal investigator (CC) will work with the Zambian Ministry of Education, the Lusaka Teachers Association, district school boards, and heads of elementary and high schools to invite teachers to join the Wellness4Teachers email messaging program. Participants will be eligible for inclusion if they are school teachers and residents of Livingstone, Lusaka, Kasama, or Solwezi. Subscribers can unsubscribe from the program at any time by clicking the unsubscribe link associated with the messages. Based on the 10% dropout rate recorded for the Text4Hope program [51,52], the anticipated dropout rate for the email messaging program will be less than 15% [54].

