### Statistical Analysis

SPSS (version 25; IBM Corp) [80] will be used to analyze the quantitative data from the surveys. Surveys with more than 50% missing responses will not be included in the data analysis. There will be no missing data imputation, and the analysis of the included survey responses and results will be based on completed survey data. Descriptive statistics for demographic, mental health literacy, clinical, and burnout-related variables will be provided. A 2-tailed *P*≤.05 will be used to determine statistical significance for all analyses, and descriptive characteristics will be presented as percentages and numbers. A chi-square test and logistic regression analysis will be used to separately identify demographic, clinical, and work-related correlates of anxiety, depression, stress, low resilience, and burnout for elementary and high school teachers. Significant and borderline significant variables from the chi-square analysis would be used to develop multivariable binary logistic regression models to predict the adjusted odds of outcomes for the exposure of interest and each potential correlate. The impact of the email supportive messaging program in reducing moderate to high anxiety, moderate to high depression, moderate to high stress, burnout, and improving resilience among subscribers will be evaluated by comparing the mean changes in these parameters from baseline to 6 weeks, 3 months to 6 months, and 12 months using the paired *t* test. To assess the effects of the intervention against a control group, we will choose a defined period of 3 months during the study period (for instance, the beginning of January 2023 to the end of March 2023) and compare the prevalence and mean scores on standardized scales for stress, anxiety, burnout, and depression at 6 weeks for subscribers who have received the daily supportive SMS text messages for 6 weeks (the intervention group) to the baseline prevalence and mean scores on the same scales for new subscribers during the period (the control group).

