### Hypothesis

Based on the greater than 20% reduction in depression symptom scores in the intervention group compared to the control group in 2 randomized controlled trials in Ireland and Canada [56,57], and the greater than 20% reduction in anxiety symptom scores from baseline to 6 weeks and 3 months in subscribers of Text4Hope [51,52], we hypothesize that the Wellness4Teachers email messaging program will reduce the prevalence and severity of stress, burnout, anxiety, depression, and low resilience symptoms among Zambian teachers by at least 20%*.* We also hypothesize that the Wellness4Teachers email program will improve mental health literacy scores in the teachers subscribing to the program by at least 20%. In addition, we hypothesize that the prevalence of moderate to high stress, moderate to high anxiety, moderate to high depression, burnout, and low resilience would be comparable to the prevalence of these conditions reported in other jurisdictions [81,82]. Finally, we hypothesize that demographic factors, socioeconomic factors, organizational factors, and class size will be associated with burnout and other psychological disorders in teachers [16,19-23,49,58].

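### Correlates shared by a whole school are to be tested as if every teacher were independent, so their P values are somewhat too small and prevalence intervals somewhat too narrow

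*Protocol article*

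**What the plan says.** The Statistical Analysis section of the protocol article sets out the correlate analysis: "A chi-square test and logistic regression analysis will be used to separately identify demographic, clinical, and work-related correlates" of each condition, with elementary and high school teachers analysed separately. Variables that are significant or borderline in the chi-square tests go forward into multivariable binary logistic models. The same section adds that "A 2-tailed *P*≤.05 will be used to determine statistical significance for all analyses". Mean changes are compared by paired t test. No cluster term, robust standard error or random effect is named, and the Sample Size Estimation section applies no design effect.

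The Hypothesis section expects that "demographic factors, socioeconomic factors, organizational factors, and class size will be associated with burnout" and other disorders. On recruitment, the article says that subscription "will be initiated by individual teachers accepting an invitation to subscribe". The local principal investigator works with the ministry, a teachers' association, "district school boards, and heads of elementary and high schools to invite teachers to join the Wellness4Teachers email messaging program".

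The Data Collection section says that the questionnaires cover demographic and work-related variables but does not itemise them.

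**The concern.** Chi-square tests and ordinary logistic regression take each teacher as a separate piece of information. Organizational factors are common to everyone in a school, and class size is partly so. For such a factor the information comes largely from the number of schools. If colleagues' outcomes are positively correlated, the ordinary analysis understates the standard error, declares null school-level factors significant too often, and gives odds-ratio intervals that cover less than 95% of the time. The prevalence intervals are too narrow for the same reason.

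The chi-square P values also decide which variables enter the multivariable models, so the error carries into the second stage. The Discussion says that the results should shape school policy, and school-level factors are the ones a policy maker could act on.

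**Working it through.** **The plan's own figure.** The Sample Size Estimation section gives 993 completed surveys for a 3-point margin at 95% confidence, from 30,561 teachers. Taking a prevalence of 0.5 (not stated), n0 = 1.96² × 0.25 / 0.03² = 1,067.1. The finite-population formula n = n0 / (1 + (n0 − 1)/N) gives 1,031.1, so 1,032, for N = 30,561. It gives 992.6, so 993, for N = 14,205, the Lusaka teachers alone. The stated figure is therefore not reproduced from the stated population. That is a separate matter, and 993 is used below as planned. The enrolment figure does reproduce: 993 / 0.20 = 4,965.

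**Inputs from the article (Study Setting, Sample Size Estimation).**
- Lusaka: 10,822 + 3,383 = 14,205 teachers in 758 + 111 = 869 schools, or 16.3 per school.
- Lusaka secondary schools: 3,383 / 111 = 30.5 teachers per school.
- All four cities: 30,561 teachers in 1,286 + 869 + 1,234 + 770 = 4,159 schools, or 7.3 per school.
- Survey completion: 20%.

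**Assumed, not in the article:** ICC 0.02 to 0.10 and equal school sizes.

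**Respondents per school (m) if every teacher in a participating school subscribes.**
- Lusaka overall: 16.3 × 0.20 = 3.3
- Lusaka secondary: 30.5 × 0.20 = 6.1

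**Formulas.** Design effect DE = 1 + (m − 1) × ICC. For a factor constant within a school, the true two-sided error of a nominal 5% test is 2 × [1 − Φ(1.96/√DE)].

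| Setting | m | ICC | DE | True error |
|---|---|---|---|---|
| Lusaka overall | 3.3 | 0.02 | 1.05 | 5.5% |
| Lusaka overall | 3.3 | 0.05 | 1.11 | 6.3% |
| Lusaka overall | 3.3 | 0.10 | 1.23 | 7.7% |
| Lusaka secondary | 6.1 | 0.02 | 1.10 | 6.2% |
| Lusaka secondary | 6.1 | 0.05 | 1.26 | 8.0% |
| Lusaka secondary | 6.1 | 0.10 | 1.51 | 11.1% |

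**Thin spread.** If 993 respondents fall at random among all listed teachers, a respondent's school contains on average 1 + (7.3 − 1) × 993/30,561 = 1.2 respondents, or 1.5 at Lusaka school sizes. DE is then at most 1 + 0.5 × 0.10 = 1.05, and the true error is 5.0% to 5.6%.

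**Prevalence intervals.** With 993 surveys, a prevalence of 0.5 and N = 30,561, the margin is 3.06 points. Multiplied by √DE at m = 3.3, it becomes 3.13 (ICC 0.02) to 3.39 (ICC 0.10).

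**Check by simulation.** Beta-binomial outcomes were simulated with 990 teachers, an assumed prevalence of 0.35, equal school sizes and 4,000 runs per setting. At m = 5, a null school-level factor was declared significant in 7.5% of runs at ICC 0.05 and 9.4% at ICC 0.10; the formula gives 7.4% and 9.8%. A null factor varying freely within schools stayed between 4.5% and 5.4% in every setting, up to m = 20 and ICC 0.10.

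**Unequal school sizes.** These raise the error. A simulation with 993 respondents in 300 schools of unequal size (also about 3.3 each) gave 7.0% at ICC 0.02 and 8.1% at ICC 0.05.

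**The case against.** Three arguments tell against the point. First, schools are neither sampled nor allocated. Teachers subscribe individually and heads are one channel among several, so a reader who infers invitation school by school goes beyond the text. Second, an article commonly leaves item lists and cluster terms to a full protocol or analysis plan, and the work-related items may already include the school. Third, the article's own counts point to few respondents per school.

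The first and third arguments limit the size, not the mechanism: the independence assumption still fails for school-level factors if colleagues' outcomes correlate. The second stands as far as the school item goes, so its absence is something to confirm, not a shown omission. It does not remove the point, because the article goes beyond silence: it names the tests and fixes one significance threshold for all of them.

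Two stronger readings are tempting.
- **All the named tests give P values that are too small.** This is not supported. Correlates that vary between colleagues keep an error near 5%. The paired t test is affected only if colleagues' changes move together, and the article gives no evidence of that.
- **Error rates of 13% to 33%.** Simulation with unequal school sizes gives 13% for 100 schools at ICC 0.05, 21% for 50 schools at ICC 0.05, and 33% for 50 schools at ICC 0.10. But 993 surveys from 100 or 50 schools means about 10 or 20 respondents each. At 20% completion that requires about 50 or 100 subscribers per school, against an average staff of 16.3 in Lusaka and 30.5 in its secondary schools.

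The thin-spread case is uncertain too. The school and teacher counts date from 2004 to 2017, and the land areas given for Livingstone and Kasama suggest that some counts are provincial.

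**Conclusion.** The point holds for correlates that are constant within a school and for the prevalence intervals. The inflation is modest: about 5.5% to 8% overall and 6% to 11% in secondary schools for a nominal 5% test. These ranges rest on the assumed ICC, equal school sizes, Lusaka averages, full subscription within participating schools, and 20% completion. Lower uptake or a wide spread over schools brings the error back towards 5%; very unequal numbers per school push it up. The affected analyses belong to the secondary, associational objective. The evaluation of mean change by paired t test is not shown to be at fault.

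**What to change.** Confirm that the baseline survey records the teacher's school; if it does not, add one item, chosen from a list and stored as a code. Report the distribution of respondents per school. In the Statistical Analysis section, state that the correlate models are fitted with school as the cluster, by generalized estimating equations or logistic regression with cluster-robust standard errors, and that cluster-adjusted tests replace the plain chi-square P values for school-level factors, including at the screening step. Compute the prevalence intervals with school-clustered standard errors.

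The cost is at most one survey item, a change of wording, slightly wider intervals, and holding school as a code to protect confidentiality. No extra participants are needed to make the change. If respondents per school prove few, the results will hardly move, and the reported distribution will show why.

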### Study Objectives, Aims, and Purpose

The primary objective of this study is to determine how daily supportive email messages plus weekly mental health literacy information delivered via email would help improve mental health literacy and reduce the prevalence of moderate to high stress symptoms, burnout, moderate to high anxiety symptoms, moderate to high depression symptoms, and low resilience among schoolteachers in Zambia. The secondary objectives of this study are to map and determine the baseline prevalence and correlates of moderate to high stress, burnout, moderate to high anxiety, moderate to high depression, and low resilience among schoolteachers in Zambia. The specific objectives are as follows: (1) to determine the baseline prevalence and correlates of moderate to high stress, burnout, moderate to high anxiety, moderate to high depression, and low resilience among school teachers in Zambia. (2) To implement daily supportive email messages and weekly mental health literacy information delivered via email to improve mental health literacy. (3) To determine the effectiveness of implementing the Wellness4Teachers email messaging and mental health literacy program to reduce the prevalence of moderate to high stress symptoms, burnout, moderate to high anxiety symptoms, moderate to high depression symptoms, and low resilience among school teachers in Zambia.

Wellness4Teachers email messaging and mental health literacy program is anticipated to reduce the prevalence and severity of stress, burnout, anxiety, depression, and low resilience symptoms among Zambian teachers by at least 20%. Figure 1 is a conceptual framework illustrating the association between the various sociodemographic, personal, and work-related or organizational factors and stress, burnout, anxiety, and depression in teachers. The framework was based on empirical evidence, which showed a greater than 20% reduction in depression symptoms in 2 randomized controlled trials [56,57] and a greater than 20% reduction in anxiety symptom scores from baseline to 6 weeks and 3 months in subscribers of Text4Hope [51,52]. An increased number of predictors such as socioeconomic and demographic factors, workload, and poor organizational structure may correlate with the prevalence and severity of burnout and other psychological and mental health conditions experienced by teachers [3,16,19-23,49,58].

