### Sample Size Estimation

With the total teacher population in Lusaka, Livingstone, Kasama, and Solwezi of about 30,561 [66], using a web-based script [77], it is projected that the sample size needed for our prevalence estimates with 95% confidence and a 3% margin of error for moderate to high stress, burnout, moderate to high anxiety, moderate to high depression, and low resilience among teachers in Livingstone, Lusaka, Kasama, and Solwezi will be 993. Based on the maximum survey completion rate attained for the Text4Hope and Text4Mood programs in Alberta of 20% [50,78,79], to achieve an estimated 993 completed surveys at baseline, it is planned to enroll at least 4965 teachers in the Wellness4Teachers email supportive and mental health literacy messaging program within 12 months.

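### Chi-square screening, apparently run separately by school level, leaves screened-out correlates without adjusted odds ratios and misses many moderate ones among about 181 high school teachers

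*Protocol article*

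**What the plan says.** Baseline correlates of five conditions (stress, burnout, anxiety, depression, low resilience) are a secondary objective under Study Objectives, Aims, and Purpose and a secondary outcome under Outcomes and Measures. The Hypothesis section predicts which kinds of factor will be associated.

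The method is in Statistical Analysis. Chi-square tests and logistic regression are to identify separately the "correlates of anxiety, depression, stress, low resilience, and burnout for elementary and high school teachers". The entry rule follows: "Significant and borderline significant variables from the chi-square analysis would be used to develop multivariable binary logistic regression models". The same sentence says these models will give adjusted odds for the exposure of interest and for each potential correlate. A two-tailed P of .05 "will be used to determine statistical significance for all analyses", so borderline must mean something above .05, but no value is given. On incomplete records, "There will be no missing data imputation".

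Sample Size Estimation derives 993 completed baseline surveys as the "sample size needed for our prevalence estimates with 95% confidence and a 3% margin of error". It gives no sizing for regression or for either school level. The protocol already has a basis for choosing covariates in advance: Figure 1 is described as a "conceptual framework illustrating the association between the various sociodemographic, personal, and work-related or organizational factors" and four of the conditions.

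**The concern.** The rule uses the same data twice, first to decide which variables enter and then to estimate their adjusted effects. Three consequences follow from the wording alone.

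- **Missing estimates.** A factor that fails the screen never enters, so the promised adjusted odds ratio does not exist for it.
- **Incomplete adjustment.** A confounder whose crude association is masked by another factor is left out.
- **Intervals that ignore selection.** The reported intervals treat the chosen model as if it had been fixed in advance.

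Screening by chi-square also requires the mental health literacy score, a named correlate, to be cut into categories at the screening step.

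The split by school level adds a further problem. The smaller group may hold too few cases for several covariates. Two separate fits also cannot say whether a correlate differs between levels, because one P value below .05 and another above it is not a test of difference. The Conclusions section expects the results to inform resource allocation for the education sector, so a missed workload or organizational factor would matter.

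**Working it through.** **1. The plan's own figure.** For a proportion of 0.5 (assumed, not stated), n0 = 1.96² × 0.25 / 0.03² = 1067.1. With N = 30,561, n = 1067.1 / (1 + 1066.1/30,561) = 1031.1, so 1032 rather than 993. The figure 993 matches Lusaka's teachers alone (10,822 + 3383 = 14,205, giving 992.6). That is a separate matter and changes little here. I use the stated 993; 1032 would give 188 high school teachers instead of 181.

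**2. Size of the high school subset** (counts from Study Setting).
- High school or secondary: 1027 + 3383 + 656 + 509 = 5575.
- Primary or grades 1-9: 6158 + 10,822 + 5169 + 2837 = 24,986.
- Total: 30,561, the population figure in Sample Size Estimation.
- Share: 5575 / 30,561 = 18.2%. Expected completers: 993 × 0.1824 = 181.
- Range using single cities' shares: Kasama 656/5825 = 11.3%, giving 112; Lusaka 3383/14,205 = 23.8%, giving 236.

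**3. Cases available.** The single studies in Background give about 25% (stress) to 38% (anxiety). 181 × 0.25 = 45 and 181 × 0.38 = 69. At the conventional ten cases per parameter, that supports 4 to 7 parameters. At the 4% lower end quoted for depression, 181 × 0.04 = 7 cases. Pooled, 993 × 0.25 = 248 and 993 × 0.38 = 377; at 4%, 40.

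**4. Real correlates lost.** Assumptions: 20 binary candidates, 4 real with odds ratio 1.65, 30% prevalence, screen at P<.10, n = 181, 600 simulated data sets. The screen kept on average 1.8 of 4 with independent candidates and 2.7 of 4 with latent correlation 0.2. A pooled prespecified model on all 993 found about 3.7 of 4 significant.

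A hand check for an evenly split independent candidate uses SE = 1/√(n × 0.30 × 0.70 × 0.25) and ln 1.65 = 0.501.
- n = 181: SE = 0.324, ratio 1.54. Chance of P<.10 = Φ(1.54 − 1.645) = 0.46, and 4 × 0.46 = 1.8. Chance of P<.05 = Φ(1.54 − 1.96) = 0.34, or about 1.4 of 4.
- n = 993: SE = 0.1385, ratio 3.62. Chance of P<.05 = Φ(3.62 − 1.96) = 0.95, or 3.8 of 4.

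The loss therefore comes mainly from splitting the sample. A full model confined to 181 teachers would not recover it.

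A second simulation (15 candidates, 5 real with odds ratio 1.5, prevalence 25% to 35%, screens at .05 and .10) gives the same picture:

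| Subset | Real correlate passes, independent | Real correlate passes, correlation 0.2 |
|---|---|---|
| High school, n = 181 | 22-35% | 41-58% |
| Elementary, n = 812 | 67-84% | 94-99% |

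**5. Intervals after selection.** In the 20-candidate setting at n = 181, nominal 95% intervals for null variables that passed the screen covered the truth 52% of the time with independent candidates and 89% with correlation 0.2. A full model gave about 94%.

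**6. False correlates.** About 10% of null variables pass a .10 screen, and 48% of their intervals then miss: 0.10 × 0.48 = 4.8% of all nulls, against 6% in the full model. With 16 nulls, that is 0.77 and 0.96 per model. The simulation gave 0.76 and 0.97.

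**The case against.** The strongest reply is that the harm is easily overstated, and much of that reply stands.

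- **Chance findings.** A reader might infer from the 52% coverage that screening over-reports chance correlates. It does not, as step 6 shows: coverage among variables that passed the screen has a different denominator from coverage among all variables.
- **Inflation.** A reader might also infer that odds ratios are generally inflated. Comparing screened-in variables with all variables suggests so, but it is an unlike comparison. Among significant variables at n = 181, the mean was 2.58 with screening and 2.90 in the full model, for a true 1.65. With correlation 0.2, screened-in variables averaged 1.85 against 1.80 in the full model in one run and 1.93 against 1.96 in another. At n = 993 the screened mean was 1.68. Inflation needs a small subset and nearly independent candidates, and the Introduction describes overlapping conditions and work factors.
- **Reading of the split.** The adverb could mean separately by condition, and the multivariable sentence names no school level. Separate analysis by level is still the most natural reading, because the two teacher groups are named in the sentence that sets up both methods.
- **Left to the analysis plan.** A covariate list or a cut-off for borderline often is. But the protocol fixes the entry rule itself, and a defined cut-off would leave the consequences in place.
- **Continuous factors.** The protocol does not say how age or class size is collected, and nothing prevents continuous entry in the logistic model. The point on categories is limited to the screening step and to scale scores.

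**Conclusion.** The concern holds in a limited form. The entry rule cannot deliver the adjusted odds that its own sentence promises, leaves masked confounders unadjusted, and yields intervals that ignore selection. Undercoverage for screened-in null variables ranges from severe (52%) to mild (89%), depending on how correlated the candidates are. In a high school subset of about 181 (112 to 236), screening would keep roughly half to two thirds of moderate correlates (1.8 to 2.7 of 4), and separate fits leave the question of differences between levels untested.

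The documents do not support the stronger claims that the method over-reports chance correlates or generally inflates odds ratios.

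The subset size assumes 993 completers and proportional uptake. The counts come from different years and mix Lusaka's secondary schools with grades 10-12 elsewhere. Enrollment may exceed the minimum, while Limitations concedes that the target may be missed. The number of candidates, odds ratios, correlation and screening cut-offs are assumptions. The change should be made, but it affects a secondary, associational objective; no primary outcome or intervention effect depends on it.

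**What to change.** For each condition, fit one pooled logistic model.

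- Fix the covariates before analysis from factors the protocol already names in Study Objectives, Aims, and Purpose, Outcomes and Measures, and Hypothesis. The Figure 1 framework, as described, does not cover low resilience, so that list must come from the other two sections.
- Set the number of parameters by the observed number of cases (or of non-cases, if fewer), not by a fixed figure. At ten per parameter, 248 to 377 cases would allow about 25 to 38; 40 cases would allow 4.
- Include school level as a covariate, with a few named interactions to test whether correlates differ.
- Enter scale scores such as mental health literacy as continuous.
- Report every coefficient with its interval, and present the chi-square results as description only.

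Pooling recovers the lost correlates. Prespecification restores the missing odds ratios and makes the intervals interpretable. The cost is analysis wording, a longer coefficient table, and the work of agreeing the list in advance. Data collection does not change.

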### Outcomes and Measures

Validated screening scales for self-reported symptoms will be used to assess clinical outcomes. These include the Mental Health Literacy Scale [69], the Generalized Anxiety Disorder 7-item (GAD-7) Scale (a GAD-7 score of ≥10 indicates moderate to high anxiety) [70], the Perceived Stress Scale (PSS-10) (a PSS-10 score of ≥10 indicates likely moderate to high stress) [71], the Brief Resilience Scale (BRS; BRS mean scores ranging from 1.00 to 2.99 indicate low resilience, scores from 3.00 to 4.30 suggest normal resilience, and mean scores from 4.31 to 5.00 suggest high resilience) [72,73], and the Patient Health Questionnaire-9 (PHQ-9; a score of ≥10 indicates moderate to high depression) [74]. Burnout will be assessed using the Maslach Burnout Inventory (MBI), specifically the MBI-Educators Survey, for use with educators [75,76]. An exploratory outcome will be to evaluate the acceptance of the Wellness4Teachers program by teachers in Zambia, which can be measured by the proportion of the target population (teachers in Livingstone, Lusaka, Kasama, and Solwezi) who subscribe to the program. Primary outcomes for this study will be changes in mental health literacy and the prevalence of moderate to high stress, burnout, moderate to high anxiety, moderate to high depression, and low resilience from baseline to 6 weeks, 3 months, 6 months, and 12 months among the subscribers of the Wellness4Teachers Zambia program. Secondary outcomes include the mean score on the Mental Health Literacy Scale and the prevalence of moderate to high stress, burnout, moderate to high anxiety, moderate to high depression, and low resilience at baseline in subscribers of the Wellness4Teachers email messaging program. Other secondary outcome measures will include changes in mean scores on the PSS-10, MBI, GAD-7, PHQ-9, and BRS. In addition, sociodemographic factors, work-related factors, and mental health literacy correlate with moderate to high stress, burnout, moderate to high anxiety, moderate to high depression, and low resilience at baseline among subscribers of the Wellness4Teachers program.

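### The longitudinal impact analysis tests mean changes, which the plan lists as secondary, and leaves out mental health literacy; the primary prevalence outcomes have no matching analysis of change among subscribers

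*Protocol article*

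**What the plan says.** In the protocol article, Outcomes and Measures sets the primary outcomes: "Primary outcomes for this study will be changes in mental health literacy and the prevalence of moderate to high stress, burnout", followed by anxiety, depression and low resilience. The changes run "from baseline to 6 weeks, 3 months, 6 months, and 12 months among the subscribers". Mean scores have a lower rank in the same section: "Other secondary outcome measures will include changes in mean scores on the PSS-10, MBI, GAD-7, PHQ-9, and BRS".

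The Hypothesis section expects a reduction of at least 20% in both the prevalence and the severity of the five conditions. Separately, it expects the program to "improve mental health literacy scores in the teachers subscribing to the program by at least 20" percent.

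The Statistical Analysis section describes the impact of the program "in reducing moderate to high anxiety, moderate to high depression, moderate to high stress, burnout, and improving resilience among subscribers" and says that it "will be evaluated by comparing the mean changes in these parameters from baseline to 6 weeks, 3 months to 6 months, and 12 months". The method it names for this is a paired t test. Three other parts of that section bear on the point:

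- Mental health literacy is named only among the variables to be described.
- Chi-square tests and logistic regression are assigned to finding correlates, not to change over time.
- A control comparison sets prevalence and mean scores at 6 weeks, for stress, anxiety, burnout and depression, against the baseline values of new subscribers. No test is named.

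**The concern.** The outcome section and the analysis section disagree about what is tested. A primary outcome defined as a change in a proportion needs an analysis of that proportion. The analysis given compares means, and changes in mean scores are listed as secondary. Literacy, the first-named primary outcome, has a numerical hypothesis but no inferential analysis.

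Two consequences follow. A significant shift in a mean score could be reported as a fall in the prevalence of moderate to high symptoms, which it does not by itself establish; the Hypothesis section sets the 20% target for prevalence and severity separately. And the choice of method for the primary outcomes would be left open until the data are in hand, which invites selective reporting.

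**Working it through.** The plan states no figure for this point, so the check sets the sections side by side.

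| Item | Outcomes and Measures | Statistical Analysis: impact sentence | Statistical Analysis: control comparison |
|---|---|---|---|
| Stress, burnout, anxiety, depression | Primary: change in prevalence | Mean changes, paired t test | Prevalence and means, 6 weeks only |
| Low resilience | Primary: change in prevalence | Mean changes, paired t test | Not included |
| Mental health literacy | Primary: change | Not included | Not included |
| Mean scores on the five scales | Secondary: change | Mean changes, paired t test | Means for four conditions, 6 weeks only |
| Time contrasts | Baseline to each of four follow-ups | Baseline to 6 weeks; 3 to 6 months; 12 months (as written) | 6 weeks against another group's baseline |

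**Prevalence.** The impact sentence fits the secondary row. No method for paired binary data is named in the section.

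**Does the alternative reading rescue it?** Suppose the parameters were 0/1 indicators of being a case. With n pairs, let b be the number who go from case to non-case and c the number who go the other way. The mean within-person change is (c − b)/n, which is the change in prevalence among those pairs. The paired t statistic divides this by its standard error, about √{[(b + c)/n − ((c − b)/n)²]/n}. McNemar's statistic is (c − b)/√(b + c). The two are close when (c − b)²/n is small beside b + c. So a paired t test on indicators would be a workable analysis of prevalence change in a large sample. The text does not say that indicators are meant, and a paired t test of mean changes is ordinarily an analysis of scores.

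**Literacy.** The impact sentence lists its five outcomes by name, and literacy is not one of them. The control comparison lists four, and literacy is again absent. What remains is description, so the 20% hypothesis has no stated test at any of the four follow-ups.

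**Control comparison.** It covers four of the five conditions at one of four follow-ups, and compares different people. It cannot supply change among subscribers at 3, 6 or 12 months, and it says nothing on low resilience.

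**Contrasts.** Read literally, the impact sentence adds a 3-to-6-month contrast and drops both baseline to 3 months and baseline to 6 months. The Abstract, Data Collection, Outcomes and Measures and Limitations sections all give the same four follow-ups. The likeliest explanation is a stray word in a list of four time points.

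**The case against.** The strongest reply has four parts.

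1. *Prevalence is not absent from the analysis.* This is right: the control comparison does compare it. A reader might infer that prevalence is nowhere compared, and the text does not support that. What stands is that this comparison is not the change among subscribers that the primary outcome describes.
2. *The sentence names dichotomised states, so its mean changes could be changes in 0/1 indicators.* This is possible, as the algebra shows. It therefore rules out the strong claim that no primary contrast could have any matching analysis. It does not remove the ambiguity, and it does nothing for literacy.
3. *The paired t test on scores is legitimate.* It is, for the severity hypothesis and the secondary outcomes. The objection to it is only that it stands where the primary analysis should be.
4. *A condensed article may leave the test for each outcome to an analysis plan.* That would excuse silence. Here the article names an impact analysis, and the analysis does not fit its own primary outcomes.

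A reader might also infer that baseline to 3 months is deliberately untested. The four follow-ups given consistently elsewhere point to a slip, so this is wording to correct. Nor should one put a figure on how far mean and prevalence results would diverge: the article gives no score distributions for these teachers, and the scales do not share one cut-off.

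**Conclusion.** The point holds as an internal contradiction in the protocol article. The literacy limb is the firmest: a primary outcome with its own 20% hypothesis has no inferential analysis. The prevalence limb rests on reading mean changes as changes in scale scores, which is the natural but not the only reading. On that reading, all five primary prevalence outcomes lack an analysis of change among subscribers, and the one prevalence comparison (four conditions, 6 weeks, different people) does not fill the gap. The contrast wording is a minor matter of reconciliation. This should be settled before any follow-up data are analysed, because as written the primary outcomes are not tested as defined.

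**What to change.** In the Statistical Analysis section:

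- For each of the five primary prevalence outcomes, compare baseline with each of the four follow-ups by a paired binary method: McNemar's test, or logistic regression for repeated measures (GEE or mixed model). Report the change in percentage points with a 95% confidence interval.
- Add the Mental Health Literacy Scale score to the paired analysis, or use a linear mixed model, at the same four contrasts.
- Keep the paired t tests of mean scores and label them secondary.
- Rewrite the time contrasts to agree with Outcomes and Measures.

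McNemar's test for the prevalences and a paired test for literacy would be enough to resolve the contradiction; the regression models are an option. Adding literacy and low resilience to the control comparison is also optional. The binary analysis of burnout needs a case definition on the MBI. The article gives no cut-off, so the wording should point to wherever it is set.

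The cost is a revised paragraph and modest extra programming. The scales are already in the planned surveys, so no new data are required.
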